## Abstract

**Background:**

The current standard treatment of patients with relapsed or refractory diffuse large cell B-Cell lymphoma (DLBCL) primarily consists of intensified salvage therapy and, if the disease is chemo-sensitive, high dose therapy followed with autologous stem cell transplantation. In the rituximab era however, this treatment approach has shown only limited benefit. In particular, patients relapsing after rituximab-containing primary treatment have an adverse prognosis, especially if this occurs within the first year after therapy or if the disease is primarily refractory. Therefore there is an ultimate need for improved salvage treatment approaches.

**Methods/design:**

The STORM study is a prospective, multicentre phase I/II study to evaluate the safety, feasibility and activity of salvage therapy consisting of the mTOR inhibitor temsirolimus added to the standard therapy rituximab and DHAP for the treatment of patients with relapsed or refractory DLBCL. The primary objective of the phase I of the trial is to establish the maximum tolerated dose (MTD) of temsirolimus in combination with rituximab and DHAP. The secondary objective is to demonstrate that stem cells can be mobilized during this regimen in patients scheduled to proceed to high dose therapy. In phase II, the previously established maximum tolerated dose of temsirolimus will be used. The primary objective is to evaluate the overall response rate (ORR) in patients with relapsed DLBCL. The secondary objective is to evaluate progression free survival (PFS), overall survival (OS) and toxicity. The study will be accompanied by an analysis of lymphoma subtypes determined by gene expression analysis (GEP).

**Discussion:**

The STORM trial evaluates the safety, feasibility and activity of salvage therapy consisting of the mTOR inhibitor temsirolimus added to standard therapy of rituximab and DHAP for the treatment of patients with relapsed or refractory DLBCL. It also might identify predictive markers for this treatment modality.

**Trial Registration:**

ClinicalTrials.gov NCT01653067

## Background

Non-Hodgkin’s Lymphomas are the fifth most common tumor type worldwide, and their incidence is still increasing [1]. Although in recent years advances in tumor therapy and supportive care have improved overall survival, a large proportion of patients will ultimately die of their disease. The prognosis of diffuse large B-cell lymphoma (DLBCL) has improved with the advent of the monoclonal antibody rituximab. However, there is increasing evidence that treatment of patients with relapsed and refractory disease remains challenging. The current standard treatment of patients with relapsed or refractory DLBCL primarily consists of intensified salvage therapy using widely accepted regimens like R-DHAP or R-ICE. For chemo-sensitive disease high dose therapy followed with either autologous [2] or, in selected cases, allogeneic transplantation is applied. In the rituximab era however, high dose therapy and autologous transplantation have only been of limited benefit in relapsed and refractory disease, and allogeneic transplantation is limited to a selected small subset of patients. The dismal prognosis was recently underlined by the interim analysis of the CORAL trial, in which patients with relapsed DLBCL were randomized to either receive salvage R-DHAP or R-ICE: it was demonstrated that patients relapsing after rituximab-containing primary treatment had an adverse prognosis, especially if this occured within the first year after therapy or if the disease was primarily refractory. Even with this intensive treatment in this patient subset only 10-15% of patients achieve long-term survival [3].

Recently, the specific mTOR inhibitor temsirolimus has shown to be clinical active in relapsed mantle cell lymphoma in a large multicenter phase III trial, which included patients with up to 7 prior lines of therapy. In this poor-risk population, the ORR was 22% using a regimen consisting of 175 mg temsirolimus for 3 weeks given weekly, followed by 75 mg/weekly or 25 mg/weekly until tumor progression or unacceptable toxicity occured. During the later therapy phase the average dose was 52 mg/week. The most prominent side effect in this trial was thrombocytopenia. PFS, which was the primary endpoint of this trial, was significantly superior using this regimen, in comparison to a standard treatment arm, which consisted of a variety of commonly accepted single agents. Interestingly, the superiority of temsirolimus appeared to be accentuated in patients with a lower number of pre-treatments [4]. In another trial, the combination of rituximab and even low dosis of temsirolimus resulted in impressive response rates in relapsed and refractory mantle cell lymphoma [5].

Furthermore, a recently presented phase II trial by Smith and colleagues demonstrated single agent activity of temsirolimus in DLBCL and follicular lymphoma by achieving a ORR of 56% in relapsed patients. Especially a single agent activity of 28% in relapsed aggressive lymphoma is promising and merits further evaluation [6].

It seems therefore a logical consequence to incorporate temsirolimus into earlier treatment lines or to combine it with other therapies. Accordingly, a combination of temsirolimus with bendamustine and rituximab achieved a response in all patients evaluable with relapsed mantle cell and follicular lymphoma [7]. Of note, in recent in vitro experiments, additive action of temsirolimus, dexamethasone, cytarabine and platinum could be demonstrated [8]. Building on to this, the STORM trial combines temsirolimus with a well-established salvage treatment protocol (R-DHAP) with a known safety profile for the treatment of patients with refractory or relapsed DLBCL. The aim of this trial is to determine the safety, feasibility and clinical activity of the proposed regimen.

### On-site monitoring

During recruitment on-site monitoring is performed following good clinical practice (GCP) guidelines. The data management will be performed by the Interdisciplinary Centre for Clinical Trials (IZKS) at the University of Mainz.

### Ethics, informed consent and safety

The final protocol was jointly approved by the central ethics committee of this trial at the University of Heidelberg, Medical School (AFmu-017/2012, http://www.klinikum.uni-heidelberg.de) and by the ethics committees of all participating centres. This study complies with the Helsinki Declaration in its most recent German version, the Medical Association's professional code of conduct, the principles of Good Clinical Practice (GCP) guidelines and the Federal Data Protection Act. The trial will also be carried out in keeping with local legal and regulatory requirements. The medical secrecy and the Federal Data Protection Act will be followed.

Informed consent is obtained from each patient in oral and written form before inclusion in the trial and after the nature, scope, and possible consequences of the trial have been explained by a physician. The investigator will refrain from any measures specifically required only for the clinical trial until valid consent has been obtained.

### Study design and objectives

The STORM study is a prospective phase I/II study to evaluate the safety, feasibility and activity of a salvage therapy consisting of the mTOR inhibitor temsirolimus added to standard therapy of rituximab and DHAP for the treatment of patients with relapsed or refractory DLBCL. The STORM-trial consists of two phases.

Phase I is a dose-escalation study of temsirolimus. The primary objective is to establish the maximum tolerated dose (MTD) of temsirolimus in combination with rituximab and DHAP. The secondary objective is to demonstrate that stem cells can be mobilized during this regimen in patients scheduled to proceed to high dose therapy.

In phase II, the previously established maximum tolerated dose of temsirolimus will be used. The primary objective is to evaluate the overall response rate (ORR) in patients with relapsed DLBCL. The secondary objective is to evaluate progression free survival (PFS), overall survival (OS) and toxicity.

### Patient selection

To be included into the STORM trial, patients must be at least 18 years old and have a histologically confirmed diagnosis of DLBCL according to the World Health Organization classification. There must be a documented relapse or progression after at least one prior treatment but a maximum of two prior treatments. Prior treatment must have included at least three cycles of anthracycline-containing chemotherapy (e.g. CHOP-like). The histology has to be confirmed by a reference pathologist. Evaluation of CD20 status is compulsory. At least one measurable tumor mass (>1.5 cm x >1.0 cm), involvement of any organ or bone marrow infiltration must be present. In addition, adequate organ function and a Eastern Cooperative Oncology Group [ECOG] performance Status of less than 3 are essential for inclusion into the trial. Patients are required to use adequate contraception before entry and throughout the study, if appropriate. Naturally, patients must have signed an informed consent document indicating that they understand the purpose of and procedures required for the study and are willing to participate in the study.

Patients with lymphoma other than DLBCL or active central nervous system lymphoma are not eligible. Other exclusion criteria are severe concomitant diseases, active uncontrolled infections including HIV, active hepatitis B or C or other malignant disease (except: adequately treated non-melanoma skin cancer, curatively treated in-situ cancer of the cervix, DCIS of the breast, or other solid tumors curatively treated with no evidence of disease for >5 years). Prior treatment with temsirolimus, known CD20 negativity, disease refractory to DHAP in a prior treatment line, severe psychiatric illness, peripheral neuropathy or neuropathic pain grade 2 or worse, prior autologous or allogeneic stem cell or bone marrow transplantation, concurrent treatment with another investigational agent during the conduct of the trial or known intolerance to sirolimus or derivates, cytarabine, cisplatine or rituximab will prohibit inclusion, as well as pregnancy or breast feeding.

### Statistical design

In phase I of the study, a 6 + 6 standardized design is chosen to establish the MTD of the investigational product (temsirolimus). A maximum of 48 patients can consequently be included into this phase. In phase II of the study, 40 patients will be included, receiving two to four cycles of the full target dose of temsirolimus in combination with R-DHAP, as established in phase I of the trial. The number of cycles will depend on the evaluation of activity and toxicity of the regimen by the investigator in each individual patient. Based on published data on rituximab in combination with DHAP, a response rate of at least 60 to 65% (40% CR and CRu) can be expected. The study will be terminated if the number of non-responders exceeds a critical value determined by Wald´s Sequential probability ratio test. In both phases of this trial explorative statistics are used to calculate remission and response rates. Median progression free survival, overall survival etc. are calculated by the Kaplan and Meier method. Adverse events will be classified according to MedDRA terminology. The frequency of adverse events will be calculated, and there will be further analyses to determine their seriousness, intensity, duration, relationship to trial treatment, actions taken and clinical outcome. Patients with and without consolidating high dose therapy and autologous stem cell transplantation will be analysed separately.

### Work up

Patients with histologically documented diagnosis of DLBCL receive a complete work-up which includes cervical, thoracic, abdominal and pelvic CT scans, bone marrow histology and extensive laboratory testing. The IPI risk score will be calculated for each patient. All in- and exclusion criteria are evaluated. If patients meet all inclusion criteria, they will be informed about the study and all associated risks and benefits, and their written consent is sought. If patients decline treatment within the STORM trial, an adequate alternative treatment regimen is offered.

### Treatment

This is a multicenter, open label, single arm, phase I/II study. Placebo will not be used within this trial. In phase I, the dose escalation phase of this trial, 6 patients will be included in each dose level. There will be four cohorts, administering up to a maximum of four cycles with 25 mg, 50 mg, 75 mg or 100 mg temsirolimus on day 1 and 8 in combination with rituximab (375 mg/m^2^ day 2) and DHAP (dexamethasone 40 mg day 3–6, cisplatin 100 mg/m^2^ day 3, cytarabine 2 × 2 g/m^2^ day 4). Treatment is repeated on day 22 for up to a maximum of 4 cycles.

After inclusion of six patients, each patient has to receive at least one complete cycle without experiencing any dose limiting toxicity, until the enrolment into the next cohort can be initiated. In phase II of the trial 40 patients will be included to receive the previously established full target dose. Special attention in phase I and phase II of the study is brought to monitoring of adverse events. Stem cell mobilization and subsequent high dose therapy and autologous stem cell transplantation can be performed in eligible patients (Figure 1).

**Figure 1 F1:**
[figure not shown]
Treatment algorithm of the STORM trial.

### Safety and discontinuation of treatment

Toxicities are classified by grade, type, duration, onset, and relationship to study treatment using the NCI Common Toxicity Criteria (CTC). Dose limiting toxicities of STORM in the context of the trial treatment are defined as any CTCAE grade V toxicity that are potentially related to the trial treatment, any hematological toxicity not recovering to at least NCI CTCAE grade II after 28 days after start of the last STORM-cycle (except as a consequence of bone marrow insufficiency due to bone marrow infiltration) and any non-hematological toxicity NCI CTCAE grade III/IV not recovering to grade II within 14 days after initial occurrence and potentially related to the trial treatment.

In phase I of the trial 6 patients will be included at each dose level. After inclusion of six patients, each patient has to receive at least one complete cycle without experiencing any dose limiting toxicity (DLT), until the enrolment into the next cohort can be initiated. If one DLT occurs, this is discussed with the data safety monitoring board (DSMB). The DSMB may recommend that six additional patients will be added to the specific dose level. If two DLTs occur in the first six patients of a cohort, six additional patients will be added to the specific dose level and this will be discussed with the DSMB. If three DLTs occur in the 6 + 6 cohort, the DSMB will be informed and will recommend further action. If a fourth DLT appears in the 6 + 6 cohort, the last dose level with three or less than three DLTs will be considered the standard dose for the phase II trial. If four DLTs occur in cohort A, the study will continue with an additional Cohort X with a temsirolimus dose of 15 mg. If the final dose level is achieved without any DLT, there will be no further dose escalation. Additionally, cumulated data of each dose level will be presented to the DSMB prior to proceeding to the next dose level. The 6 + 6 design was chosen to provide a more robust data basis than a 3 + 3 design.

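### The written minimum for opening the next dose cohort, one 21-day cycle without a DLT, is shorter than the 28-day and 14-days-from-onset clocks that define a DLT.

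*Protocol article*

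**What the plan says.** All of this is in the protocol article.

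- **Schedule** (Treatment): temsirolimus is the only escalated drug, given at "25 mg, 50 mg, 75 mg or 100 mg temsirolimus on day 1 and 8 in combination with rituximab" and DHAP. "Treatment is repeated on day 22 for up to a maximum of 4 cycles", so one cycle is 21 days.
- **Escalation condition** (Treatment, repeated under Safety and discontinuation of treatment): after six patients are included, "each patient has to receive at least one complete cycle without experiencing any dose limiting toxicity, until the enrolment into the next cohort" may begin.
- **DLT definition** (Safety and discontinuation of treatment), three kinds: related grade V toxicity; "any hematological toxicity not recovering to at least NCI CTCAE grade II after 28 days after start of the last STORM-cycle", except where marrow infiltration explains it; and related grade III/IV non-haematological toxicity "not recovering to grade II within 14 days after initial occurrence".
- **Count rules** (same section): a single DLT goes to the DSMB, with expansion left open: "The DSMB may recommend that six additional patients will be added to the specific dose level". With a second DLT the expansion becomes mandatory: "If two DLTs occur in the first six patients of a cohort, six additional patients will be added to the specific dose level". A fourth DLT in the 6 + 6 cohort stops escalation.
- **Oversight** (same section): "Toxicities are classified by grade, type, duration, onset, and relationship to study treatment", and the DSMB is shown cumulated data for each dose level before the next one starts. No minimum follow-up is given for that review.

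**The concern.** The escalation condition and the DLT definition run on different clocks. A haematological DLT cannot exist by day 21, so for that class the one-cycle condition is met automatically. The Background names thrombocytopenia as the most prominent side effect of temsirolimus in the mantle cell trial, so this is an expected toxicity class. For non-haematological events, only onsets in the first week of the cycle can be classified in time. No non-fatal toxicity starting on or after the second temsirolimus dose can be called a DLT within the cycle on which escalation depends.

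Two things are at stake. New patients could receive a higher dose before the current level has been judged by the trial's own definition. And because the response depends on the count (one DLT: discretionary expansion; two: mandatory), one called plus one pending DLT would be handled as one.

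**Working it through.** **Check on the design as read.** Four dose levels x (6 + 6) = 48, which matches the stated phase I maximum.

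**Day counts (no assumptions).** The cycle is days 1-21.

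- Haematological: the call comes 28 days from cycle start; 28 - 21 = 7 days after the cycle ends.
- Non-haematological: onset on day d is callable on day d + 14.

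| Onset day | Callable on day | Days past day 21 |
|---|---|---|
| 1 | 15 | 0 |
| 7 | 21 | 0 |
| 8 | 22 | 1 |
| 14 | 28 | 7 |
| 21 | 35 | 14 |

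So by day 21 only grade V events and non-haematological onsets on days 1-7 can be called.

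**How many patients are open (assumes even accrual over both phases).** Phase I takes 24 to 48 patients and phase II 40, so 64 to 88 in 24 months (730.5 days). Spacing is 730.5/64 = 11.4 to 730.5/88 = 8.3 days. When patient 6 reaches day 21:

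- patient 5 is at day 32.4 to 29.3: haematological clock closed, non-haematological onsets from about day 19 or 16 still open;
- patient 4 is at day 43.8 to 37.6: nothing from cycle 1 open.

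Pauses between cohorts would shorten spacing within a cohort and leave more patients open.

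**Illustration.** Let p be the DLT rate, q = 1 - p, and v6 and v5 the shares of DLTs in patients 6 and 5 that are callable by then. Patients 1-4 are fully observed. None of p, v6 or v5 comes from the protocol.

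*(a) At least one DLT pending, given none visible:* 1 - [q/(1 - p·v6)] x [q/(1 - p·v5)].

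For p = 0.33, v6 = 0.5, v5 = 1: 1 - 0.67/0.835 = 0.198.

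*(b) At most one visible but two or more in truth.* Write a6 = p(1 - v6) and a5 = p(1 - v5) for pending, and b6 = p·v6 and b5 = p·v5 for visible:

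4pq³ x (a6·q + a5·q + a5·a6) + q⁴ x (b5·a6 + a5·b6 + a5·a6).

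With v5 = 1 this reduces to 5pq⁴·a6.

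- p = 0.33: 5 x 0.33 x 0.67⁴ x 0.165 = 0.055.
- p = 0.10: 5 x 0.10 x 0.9⁴ x 0.05 = 0.016.
- p = 0.33, v5 = 0.9: 0.397 x 0.1381 + 0.2015 x 0.0599 = 0.067.
- p = 0.10, v5 = 0.9: 0.2916 x 0.0545 + 0.6561 x 0.0055 = 0.020.

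Results for v6 = 0.5; in each pair the first figure is for v5 = 1 and the second for v5 = 0.9:

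| p | (a) pending, none visible | (b) two-DLT trigger not seen |
|---|---|---|
| 0.10 | 5.3%, 6.3% | 1.6%, 2.0% |
| 0.25 | 14.3%, 17.0% | 4.9%, 6.0% |
| 0.33 | 19.8%, 23.5% | 5.5%, 6.7% |
| 0.40 | 25.0%, 29.7% | 5.2%, 6.4% |

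At p = 0.33, moving v6 to 0.75 gives (a) 11.0%, 15.1% and (b) 2.7%, 3.9%. Moving it to 0.25 gives (a) 27.0%, 30.4% and (b) 8.2%, 9.5%.

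**What (b) consists of.** With only patient 6 open, every such cohort has exactly one visible DLT. With patient 5 also open, two pending and none visible has probability q⁴·a5·a6. At p = 0.33 that is 0.2015 x 0.033 x 0.165 = 0.0011, about 0.1% of cohorts.

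**The case against.** The strongest defence is that the protocol nowhere says escalation opens on day 21. A complete cycle is not defined in days, the minimum is only a minimum, and a patient with an open grade IV event arguably cannot yet be declared free of a DLT. That reading is sensible, but it is unwritten. The phrase about the last cycle also makes it harder to apply: taken as the final one of four, which would start on day 64, the haematological call would fall on about study day 64 + 28 = 92.

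Second, the DSMB must see cumulated data before each escalation, and toxicities are recorded with grade, onset and duration. It would probably see an open event and could hold escalation. This stands and lowers the practical risk. It does not remove the mismatch, because nothing tells the DSMB to wait until the event can be classified.

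Third, a condensed article may leave the DLT observation period to the full protocol. That would answer a complaint about missing detail. Here the cycle length, the escalation condition and both clocks are all printed, and they do not fit together.

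A reader might go further and infer that the MTD will be set too high. The document does not support that: no deadline stops a late DLT from counting towards the two-, three- and four-DLT rules. Nor does it support the inference that expansions will commonly be missed. Nearly all cohorts with an unseen second DLT already have one visible DLT, which by rule goes to the DSMB with expansion as an option.

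**Conclusion.** The point holds as a conflict between printed safety rules. The day counts need no assumptions: the written minimum ends 7 days before the haematological clock and up to 14 days before the non-haematological one. The consequence is a possible one- to two-week early opening of a higher dose, normally concerning the last-enrolled patient.

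The frequencies are illustrative only. They rest on even accrual, an assumed DLT rate and assumed callable shares. The 33% rate equals four DLTs in twelve, the protocol's own stopping count, so it marks a level at the edge of tolerability; 10% is more plausible for the lower doses. The figures also take no account of the DSMB acting on open events, which would reduce the effect. The point is worth correcting because the rule protects patients and the correction is cheap.

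**What to change.** Add to the escalation rule that the DSMB escalation review is held, and the next cohort opens, only when both conditions are met:

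1. every patient in the cohort has either reached 28 days from the start of cycle 1 or has no haematological toxicity above grade II at the end of that cycle; and
2. any grade III/IV non-haematological toxicity from cycle 1 has recovered to grade II or reached 14 days from onset.

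State also that, for this decision, the last cycle in the haematological definition means cycle 1.

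The cost is one or two sentences. Waiting grows by 7 days for an open haematological toxicity and by at most 14 days for a non-haematological event starting on day 21. There is no extra wait when nothing is open at the end of the cycle.
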